### Follow-up

Participants are followed up via study questionnaires at 2 weeks, 6 weeks, 3 months, and 12 months after surgery. In 2-week follow-up, the wound recovery, blood transfusion volume, and VAS score of the affected limb are recorded. In a 6-week follow-up, quadriceps function is evaluated by isokinetic muscle strength testing, three-dimensional gait analysis, and posture stability testing. KSS, WOMAC, and postoperative satisfaction score are recorded 3 and 12 months after surgery. Complications are recorded in every follow-up.

### Data collection and management

All the data should be collected timely, correctly, and completely in the case report form. The stiffness and thickness of the quadriceps muscle are collected by ultrasound researchers. The isokinetic muscle strength tests, three-dimensional gait test, and balanced postures test are collected by rehabilitation researchers. The rest of the outcomes are collected by orthopedic researchers. All the data is stored in the database and processed by Microsoft Excel®.

The data management committee consisting of orthopedic surgeons, statisticians, and administrative staff is established to assess the progress of this study, so as to ensure the safety of study participants and to maintain the study’s scientific integrity.

### Auditing and amendments

To guarantee the quality of trial conduction, experts independent of this trial will be invited to audit the trial implementation process every 2 months. The experts may have access to source documents and study records to ensure the quality of trial conduct. There is no interim analysis in this study. Major amendments to this study protocol will be communicated with investigators, trial regulators, journals, and the ethics committee.

### Statistical analysis

The statistician who conducted the analysis is blinded to the group allocation. Summary statistics are used to describe the participant characteristics of the trial groups at baseline in the intention-to-treat (ITT) analysis set. The missing data of quadriceps thickness and stiffness is imputed by the multiple imputation method. The results of multiple imputation data are used as a type of sensitivity analysis for comparing primary outcomes between the groups.

For primary outcomes comparison, the ITT analysis is performed to evaluate the differences between the groups, and effective analysis population (EAP) and per-protocol (PP) analyses are also performed for sensitivity assessment. The primary outcomes do not follow the Gaussian distribution and are presented as median (IQR) and tested by the Mann-Whitney *U* test. Bonferroni correction is used to reduce the significance level. The means (95% CIs) of the between-group differences of the medians are calculated by the bootstrap method (1000 replications). The generalized linear mixed models (GLMM) are also performed for the primary endpoint, including group, gender, age, height, and weight as fixed covariates.

For comparing the secondary and exploratory endpoints, continuous data are presented as means (SDs) or medians (IQRs) as appropriate. The secondary endpoints are analyzed by the linear mixed model (LMM), adjusted for gender, age, height, weight, and other covariates. The correlation type of different measurement time points is assumed as the first-order autocorrelation in the LMM. Exploratory endpoints are compared by the Mann-Whitney *U* test, and the significance level is submitted to Bonferroni correction.

For safety endpoints, categorical data are presented as counts and percentages and tested by the Pearson’s chi-square test or Fisher’s exact test. The 95% CIs of absolute risk differences between the groups are calculated by the Newcombe-Wilson Score method. All statistical analyses are conducted with the statistical package SPSS, V.18.0 (SPSS Inc.) and the R 3.4.0 software. Besides Bonferroni correction, statistical significance is defined as *p* < 0.05with two-sided testing.

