**Methods:**

A prospective, single-blind, randomized controlled trial will be adopted. The target sample is 130. Patients who meet the eligibility criteria will be randomly allocated to the tourniquet group and non-tourniquet group. The primary outcome is quadriceps thickness evaluated by ultrasound test. Secondary outcomes include quadriceps stiffness, rehabilitation outcomes, operation time, intraoperative and postoperative blood loss, blood transfusion rate, thigh circumference, VAS score, opioid consumption, d-dimer and C-reactive protein level in the serum, knee function score, postoperative satisfaction score, and complications.

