#### Secondary outcomes

##### Quadriceps stiffness

Quadriceps stiffness is also evaluated in lower extremity ultrasonography before and 3 days after surgery. With the method of shear wave elastography (SWE), the muscle shear wave propagation velocity (m/s) along the long and short axis in the same section is measured 5 times, and its median is taken as quadriceps stiffness. The occurrence of venous thrombosis is detected simultaneously.

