### Sample size estimation

The primary hypothesis of this trial based on our previous pilot study is that quadriceps thickness in the tourniquet group is not less than that in the non-tourniquet group. The risk of class I error of the hypothesis is controlled within 5% during sample size estimation (*α* = 0.05).

Quadriceps thickness is 3.1 ± 0.5 cm in the non-tourniquet group and 3.1 ± 0.6 cm in the tourniquet group. Non-inferiority margin (*σ*) is 0.31, which is 10% of the average quadriceps thickness in the non-tourniquet group, *α* = 0.025 (unilateral), *β* = 0.2. We apply the non-inferiority test by PASS14 and find that we need at least 51 participants in each group. We determine that a total of 51 participants per group would have an 80% statistical power in detecting a tourniquet impact between the two groups. This will result in a total of 102 participants. Estimating that 30% of participants would drop out, a sample size of 130 participants is considered to be adequate for this study.

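### The analysis section puts an unspecified Bonferroni correction on plural, unnamed primary outcomes, while the rest of the protocol has one primary outcome, thickness, sized at an undivided one-sided 0.025

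*Protocol article*

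**What the plan says.** **Outcome definitions.** The abstract (Methods) states: "The primary outcome is quadriceps thickness evaluated by ultrasound test. Secondary outcomes include quadriceps stiffness". The Primary outcome section describes thickness alone, measured before surgery and on day 3. Study design and Sample size estimation both put the primary hypothesis on thickness alone, and the Discussion also names thickness as the primary outcome. Stiffness is described under Secondary outcomes: "Quadriceps stiffness is also evaluated in lower extremity ultrasonography before and 3 days after surgery".

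**Sample size estimation.** Thickness is the only variable used. The margin is 0.31 cm, "which is 10% of the average quadriceps thickness in the non-tourniquet group, *α* = 0.025 (unilateral), *β* = 0.2". No division of alpha is mentioned.

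**Statistical analysis.** The first paragraph says "The missing data of quadriceps thickness and stiffness is imputed by the multiple imputation method" and continues "The results of multiple imputation data are used as a type of sensitivity analysis for comparing primary outcomes between the groups". The second paragraph keeps the plural for the primary outcomes, assigns them the Mann-Whitney U test and adds "Bonferroni correction is used to reduce the significance level". It ends by applying a generalized linear mixed model to the primary endpoint, in the singular. The third paragraph gives secondary endpoints a linear mixed model and gives exploratory endpoints their own Bonferroni correction. The section closes with two-sided 0.05 wherever Bonferroni does not apply.

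**The concern.** One outcome, compared once after surgery between two arms, gives one primary test, and Bonferroni changes nothing for one test. The correction in the primary paragraph therefore presupposes at least two tests that the outcome sections do not define. It cannot be read as meant for the exploratory endpoints, because they have their own sentence in the next paragraph.

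Thickness and stiffness are the only outcomes imputed, and the stated purpose is the primary comparison. Stiffness is thus the most likely second member of the family, although the text does not say so.

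Two things are at stake:

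- **Thickness.** Followed literally, the analysis section tests it at a stricter level than the trial was sized for, so a borderline result passes or fails according to which section is applied.
- **Stiffness.** It has two candidate analyses: a Mann-Whitney test at a reduced level if it belongs to the primary family, or a covariate-adjusted linear mixed model at two-sided 0.05 if it is secondary.

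**Working it through.** **Inputs (Sample size estimation).** SD 0.5 cm without and 0.6 cm with a tourniquet; both means 3.1 cm, so the true difference is 0; margin 0.31 cm; one-sided alpha 0.025; power 80%. Allocation is 1:1, with 130 participants (65 per group) and 30% expected dropout.

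**Step 1: reproduce the stated 51 per group.**

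Normal approximation: n = (z₁₋α + z₁₋β)² × (SD₁² + SD₂²) / margin²

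= (1.960 + 0.842)² × (0.25 + 0.36) / 0.0961 = 49.8, so 50 per group.

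Noncentral t with Welch degrees of freedom, at n = 51:

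- Standard error = √(0.61/51) = 0.1094
- Noncentrality = 0.31/0.1094 = 2.835
- Degrees of freedom about 96.9, critical t = 1.985
- Power = 80.1%

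At n = 50 power is 79.3%, so 51 is the smallest n that reaches 80%. The stated figure is reproduced with one endpoint at one-sided 0.025. One-sided 0.05 would give 40 per group, and a two-test division would give 62. The design contains no Bonferroni allowance.

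**Step 2: divide alpha by two (assumed, since no divisor is stated).** One-sided alpha = 0.025/2 = 0.0125, that is 0.025 two-sided. At n = 51 the critical t rises to 2.277 with the same noncentrality.

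| Evaluable per group | Power at 0.025 | Power at 0.0125 |
|---|---|---|
| 45 (65 × 0.70 = 45.5, rounded down) | 74.9% | 64.9% |
| 51 (as sized) | 80.1% | 71.1% |
| 65 (no loss) | 88.8% | 82.3% |

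Reaching 80% at 0.0125 needs 62 per group (79.5% at 61, 80.2% at 62), or 124 evaluable in total.

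**Step 3: sensitivity to the divisor.** With three tests (0.025/3 = 0.0083), power at 51 per group is 65.5% and 68 per group are needed. The protocol does not define a family of three. The row only shows how far the answer depends on an unstated number.

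**Step 4: the band in which the sections disagree.** Under the sample-size section, thickness succeeds with one-sided p below 0.025. Under a two-test correction it needs p below 0.0125. Any one-sided p between 0.0125 and 0.025 (two-sided 0.025 to 0.05) is a success under one section and a failure under the other.

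**The case against.** **Stiffness is never called primary.** A reader might infer that the analysis section makes stiffness a co-primary outcome. The text does not support that as fact. Imputing a secondary ultrasound variable alongside the primary one does not promote it, and both the abstract and the outcomes section list it as secondary. The primary paragraph itself also uses the singular once. The plural could be loose drafting, or could refer to thickness in both legs, since the ultrasound is bilateral, or to the several analysis populations. This stands, and it is why stiffness is only apparently included. It does not rescue the paragraph: under each of these readings the correction has no stated family, and the sample size has no allowance for it.

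**The divisor may be in an analysis plan that is not shown.** A missing divisor alone would be no finding. Here, however, the article states a correction for the primary comparison, and that correction conflicts with the article's own alpha.

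**No inflation of type I error is shown.** A reader might infer that two primary outcomes at two-sided 0.05 would raise the family-wise error. The document does not describe that plan. If there are several primary outcomes, the same paragraph corrects for them; if there is one, there is no family. For thickness, the effect of an extra divisor is a stricter test and lost power.

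**The room for choice after the results is limited.** Thickness is named as the primary outcome or hypothesis in several places, and the analysing statistician is blinded. That makes a deliberate choice less likely, but it does not settle which threshold applies.

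**Conclusion.** The point holds as a contradiction between a stated multiplicity rule and the stated design. The primary family and its alpha are not fixed: the outcome and sample-size sections give one outcome at one-sided 0.025, and the analysis section gives several unnamed outcomes at an unspecified lower level.

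If the correction covers two tests, power for thickness at the planned 51 per group falls by 9 percentage points (80.1% to 71.1%). With all 65 per group evaluable it would still be 82.3%, so the loss of power depends on attrition. The ambiguity about the threshold does not.

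These figures rest on the protocol's own SDs and margin, a true difference of 0, a t-based non-inferiority test and the assumed divisor of two. The planned Mann-Whitney test is a different procedure, and its fit to a non-inferiority hypothesis is a separate matter. The point should be corrected before the analysis. It does not undermine the design if thickness is confirmed as the sole primary outcome.

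**What to change.** In the Statistical analysis section:

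1. Replace the plural with a single named primary outcome, quadriceps thickness on day 3.
2. State that it is tested at one-sided 0.025, by comparing the two-sided 95% confidence interval with the 0.31 cm margin, and delete the Bonferroni sentence for it.
3. State that stiffness is secondary and is analysed by the secondary-outcome model. Keep its multiple imputation as a sensitivity analysis of that secondary outcome.

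This is a change of wording that can be made before unblinding. It needs no further patients or data, and the 51 per group stands. The downside is that stiffness cannot support a primary claim. If the investigators do want both outcomes as primary, they must declare both, state the divided alpha and redo the sample size. For two tests, thickness alone would need 62 evaluable per group.

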**Fig. 1 Fig1:**
[figure not shown]
Flowchart of the study process

We assume the primary hypothesis of this trial is that quadriceps thickness in the tourniquet group is not less than that in the non-tourniquet group (non-inferiority study).

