### Intervention

A tourniquet is tied to patients in both groups after anesthesia so that tourniquet application is blind to patients. Tourniquet in the tourniquet group is inflated to a standard pressure of (260 ± 10) mmHg (from skin cutting to skin suture). Tourniquet in the non-tourniquet group will not be inflated. There is no concomitant intervention in this study. Proper treatment and care of participants’ combined diseases are allowed. Extra use of analgesic, anticoagulant, and anti-anemia drugs out of the study protocol is prohibited. Participants will be excluded from the trial if these drugs are necessary.

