### Adverse event management and emergency termination of the study

Adverse events in this study include, but are not limited to, myocardial infarction, pulmonary embolism, and cerebrovascular disease. Patients will be closely monitored in the study period. If there are suspicions for any adverse event, the study team will discontinue the intervention and break the blind, and patients will be treated appropriately by surgeons and internal medicine physicians. Compensation will be offered to those who suffer harm from trial participation. All adverse events will be recorded and reported in the final manuscript. If patients refuse to participate at any time point during the study, the trial of related patients will be immediately terminated. Reasons of participants who discontinue and deviate from the trial should be recorded.

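### Per-protocol has no say in the non-inferiority conclusion, although early cuff deflation can only dilute the ITT difference towards non-inferior

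*Protocol article*

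**What the plan says.** All references are to the Protocol article.

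- **Hypothesis.** Study design (text under Fig. 1) states that "quadriceps thickness in the tourniquet group is not less than that in the non-tourniquet group (non-inferiority study". Sample size estimation repeats the hypothesis and gives a margin that "is 0.31, which is 10% of the average quadriceps thickness in the non-tourniquet group".
- **Analysis sets.** Statistical analysis states: "For primary outcomes comparison, the ITT analysis is performed to evaluate the differences between the groups". In the same sentence, "effective analysis population (EAP) and per-protocol (PP) analyses are also performed for sensitivity assessment". Nothing says what follows if ITT and PP disagree.
- **Exposure.** Under Intervention, "Tourniquet in the tourniquet group is inflated to a standard pressure of (260 ± 10) mmHg (from skin cutting to skin suture"), and "Tourniquet in the non-tourniquet group will not be inflated".
- **Stopping.** Under Adverse event management, if any adverse event is suspected, "the study team will discontinue the intervention and break the blind". The rule is not written for one arm in particular.
- **Exclusion after randomization.** Intervention prohibits extra analgesic, anticoagulant and anti-anemia drugs and adds: "Participants will be excluded from the trial if these drugs are necessary".

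**The concern.** In a superiority trial, patients who do not receive the full assigned treatment make the ITT result harder to win. In a non-inferiority trial they make it easier: the arms become more alike, and a real deficit shrinks towards zero.

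Here the departure can run only one way. A cuff that was never inflated cannot be deflated early, so during surgery the stopping rule can change exposure only in the tourniquet arm, and only towards the comparator. The Discussion itself says that quadriceps injury may depend on tourniquet time, so shortened exposure matters to the question.

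At stake is a statement that a tourniquet used throughout surgery costs less than 0.31 cm of thickness. That statement could be supported by an ITT result that includes patients whose cuff was let down early, while the PP result fails the margin and has no formal weight.

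**Working it through.** **Inputs.** From Sample size estimation: SD 0.5 cm (non-tourniquet) and 0.6 cm (tourniquet), equal means of 3.1 cm, margin 0.31 cm, one-sided α = 0.025, β = 0.2, 51 per group evaluable. From Study design: 65 per group randomized. The protocol gives no rate of early deflation, so that rate is assumed.

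**The plan's own figure.** n per arm = (0.5² + 0.6²)(1.96 + 0.842)² / 0.31² = 0.61 × 7.85 / 0.0961 ≈ 49.8, so 50 by the normal formula. The noncentral t version gives 51, with power 80.2%. The stated 51 is reproduced.

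**Standard error.** SE = √(0.61/n): 0.1094 at n = 51 and 0.0969 at n = 65.

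**Dilution.** Suppose full exposure truly costs exactly the margin, so the true difference (tourniquet minus non-tourniquet) is −0.31 cm and non-inferiority should be declared only 2.5% of the time. Let q be the fraction of the tourniquet arm that is in effect unexposed. The ITT difference is then −0.31(1 − q), and

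P(declare non-inferiority) = Φ(0.31q/SE − 1.96).

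| q (assumed, tourniquet arm only) | ITT difference (cm) | n = 51 per arm | n = 65 per arm |
|---|---|---|---|
| 0% | −0.3100 | 0.0250 | 0.0250 |
| 2% | −0.3038 | 0.0285 | 0.0290 |
| 5% | −0.2945 | 0.0345 | 0.0359 |
| 10% | −0.2790 | 0.0468 | 0.0505 |

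Worked line for q = 5%, n = 51: 0.31 × 0.05 / 0.1094 = 0.142; 0.142 − 1.96 = −1.818; Φ = 0.0345.

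**Reading q.** It is not the proportion of patients whose cuff is deflated early. A patient deflated part-way has had part of the exposure. If, for illustration, the effect were proportional to time and 10% of the arm were deflated half-way, q would be 0.10 × 0.5 = 5%. An event first suspected after suture contributes nothing to q.

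The calculation uses a normal test on means with the SDs held constant, as in the sample size section. It is not the Mann-Whitney test named in Statistical analysis.

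**The case against.** The case against is substantial, and parts of it stand.

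- **PP is already planned.** True. A PP result will sit beside the ITT result, and readers will see both. What is missing is only its role in the conclusion. A rule for discordant results could be left to a separate analysis plan, but the article does more than stay silent: it assigns PP a sensitivity role, and a later plan would have to change that.
- **ITT answers a legitimate question.** It estimates the effect of assigning a tourniquet, early deflation included. That is so, but the trial describes its intervention as inflation for the whole operation, and its non-inferiority claim will be read that way.
- **The route is narrow.** This stands. Exposure ends at skin suture, the named adverse events are serious ones, and the eligibility criteria exclude severe heart disease, stroke and prior or likely thrombosis. Only an event suspected on the table can shorten exposure.
- **PP is not free of bias.** This also stands. It drops patients after randomization, possibly those with difficult surgery. It should therefore support ITT and not replace it.
- **No margin rule is stated at all.** Statistical analysis describes a two-sided Mann-Whitney test and a bootstrap interval without mentioning 0.31 cm. That ITT decides is read from the ranking of the analysis sets, not from an explicit decision rule.

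A reader might go further and infer that control-arm cuffs would be inflated when bleeding is troublesome, since a cuff is already in place. The article does not support this. It says those cuffs stay uninflated, mentions no crossover, and describes one surgeon experienced in operating without a tourniquet, with controlled hypotension and tranexamic acid for all patients. Crossover forms no part of this point.

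**Conclusion.** The point holds as a modest one. In a declared non-inferiority trial, ITT carries the primary comparison and PP has no part in the conclusion, while the one foreseeable departure during surgery favours the claim.

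The size is probably small. At 51 per arm the false non-inferiority rate is about 2.9%, 3.5% or 4.7%, against 2.5%, if 2%, 5% or 10% of the tourniquet arm are in effect unexposed. These figures rest on assumed rates, a true deficit of exactly 0.31 cm and a normal test on means.

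A reader might infer that the planned analysis is likely to give a falsely reassuring answer. The document does not show that: nothing in it supports a high rate of early deflation. The case for acting is that the direction is known and the remedy is cheap.

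**What to change.** 1. In Statistical analysis, state that non-inferiority is concluded only if the lower confidence limit for the thickness difference (tourniquet minus non-tourniquet) lies above −0.31 cm in both the ITT set and the PP set. A two-sided 95% interval matches the one-sided 0.025 used for the sample size.
2. Define PP by the cuff exposure actually received, as the Intervention section sets it out for each arm, and not by drugs taken after surgery. Need for extra drugs may itself be affected by the cuff, so selecting on it could bias PP. Patients deflated early stay in ITT in their allocated arm.
3. Reconcile the exclusion from the trial of participants who need prohibited drugs with the ITT analysis. As written, the two cannot both hold.

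**Cost.** The change is to wording, plus a record of actual inflation times if that is not already kept. No stated sample size figure changes, and with 84 participants recruited at the time of writing the rule could still be set before analysis.

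Some power is lost, because both sets must meet the margin and joint power cannot exceed that of the weaker set. By the normal formula with no true difference, power is Φ(0.31/0.1094 − 1.96) ≈ 81% at 51 per arm. If the assumed 30% dropout occurs, 130 × 0.7 = 91 remain. At about 45 per arm SE = √(0.61/45) = 0.1164, and power is Φ(0.31/0.1164 − 1.96) ≈ 76% before PP removes anyone.

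### The trial is defined and sized as non-inferiority with a 0.31 cm margin, but the primary test fixed in the analysis section is a two-sided, Bonferroni-reduced test of difference that never uses the margin

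*Protocol article*

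**What the plan says.** All references are to the protocol article.

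- **Study design, primary hypothesis (after Fig. 1).** The hypothesis is that "quadriceps thickness in the tourniquet group is not less than that in the non-tourniquet group (non-inferiority study".
- **Sample size estimation.** The margin "is 0.31, which is 10% of the average quadriceps thickness in the non-tourniquet group". Alpha is one-sided 0.025, beta is 0.2, and the calculation is a non-inferiority test in PASS. The inputs are means and SDs: "Quadriceps thickness is 3.1 ± 0.5 cm in the non-tourniquet group and 3.1 ± 0.6 cm in the tourniquet group". The result is 51 per group, raised to 130 in total for dropout.
- **Statistical analysis, primary outcome.** "The primary outcomes do not follow the Gaussian distribution and are presented as median (IQR) and tested by the Mann-Whitney" U test. The section adds that "Bonferroni correction is used to reduce the significance level", without giving the number of comparisons. Significance is otherwise two-sided at 0.05. It also plans a bootstrap 95% CI for the difference of medians and a generalized linear mixed model with group as a covariate. ITT is the main set, and "effective analysis population (EAP) and per-protocol (PP) analyses are also performed for sensitivity assessment".

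The Statistical analysis section mentions neither non-inferiority nor the margin.

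**The concern.** A non-inferiority claim needs evidence that excludes a loss as large as the margin. A test of no difference cannot supply it. Rejection says that the groups differ, and non-rejection may only mean that the data are too sparse. Under the sponsor's own planning assumption of equal means, the written test has nothing to find.

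The risk is that a non-significant p-value will be reported as showing that the tourniquet does no harm. The Pilot study section already reasons this way: from 5 knees per group without a significant difference, it infers that the tourniquet might not cause severe quadriceps injury. Any Bonferroni reduction would add to the problem, because a stricter level for a difference test makes non-significance easier to reach.

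**Working it through.** **Inputs (Sample size estimation).** SDs 0.5 and 0.6 cm, true difference 0, margin 0.31 cm, one-sided alpha 0.025, power 80%. Group sizes: 51 (stated requirement), 65 (planned enrolment), and 45 (130 × 0.7 = 91 left after the stated 30% dropout, so 45 or 46 per arm).

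**1. The plan's own figure.** n per arm = (z₀.₉₇₅ + z₀.₈₀)² × (SD₁² + SD₂²) / margin² = (1.960 + 0.842)² × (0.25 + 0.36) / 0.0961 = 49.8. With the noncentral t distribution, power is 79.4% at 50 and 80.2% at 51 per arm. The stated 51 is therefore right for a comparison of means against the margin. The same arithmetic would serve a two-sided 5% t test for a true difference of 0.31 cm. The protocol, however, assumes no difference and names a non-inferiority test.

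**2. Where the two decision criteria part.** At 51 per arm, SE = √(0.61/51) = 0.109 cm, and the 95% half-width is 1.984 × 0.109 = 0.217 cm.
- Non-inferiority needs an observed difference above -0.31 + 0.217 = -0.093 cm.
- Non-significance in the direction of harm needs only a difference above -0.217 cm (on the t scale; Mann-Whitney is close to this).
- An observed deficit between 0.093 and 0.217 cm is therefore not significant and yet fails non-inferiority.

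**3. The written test.** Simulation with normal data and the stated SDs, 20,000 or more trials per setting:

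| Per arm | Non-significant at 0.05, true deficit 0.31 cm | Non-significant at 0.025 (assumes Bonferroni over 2) |
|---|---|---|
| 45 | 27% | 38% |
| 51 | 22% | 31% |
| 65 | 13% | 20% |

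The corresponding error for the planned non-inferiority test is 2.5%. With a true difference of 0, the Mann-Whitney test rejects in about 5% of trials at each size.

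**4. Margin-based alternatives, power at a true difference of 0.**

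| Rule | 51 per arm | 65 per arm |
|---|---|---|
| 95% CI for mean difference above -0.31 | 80% | 89% |
| Margin-shifted Mann-Whitney, one-sided 0.025 | 78% | 87% |
| Bootstrap 95% CI for difference of medians above -0.31 | just under 60% | about 70% |
| Means, one-sided 0.0125 (assumes Bonferroni over 2) | 71% | 82% |

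At a true deficit of 0.31 cm, the first two rules pass in about 2.5% of trials and the bootstrap rule in about 2%.

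**The case against.** The strongest reply is that the section also plans a two-sided 95% CI and a model with a group effect. The lower limit of such a CI corresponds to one-sided 0.025, so a reader could set it against -0.31 cm. That is fair, and it limits the point in several ways.

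- A reader might infer that the trial cannot answer its own question. The documents do not support that. The data can answer it; the written primary analysis does not.
- A reader might infer that p > 0.05 is the only route to a non-inferiority claim. No section says that non-significance will be read that way, and an interval is planned. The 13% to 38% figures describe a possible misreading, not a stated rule.
- A reader might say that the median difference is on another scale than the margin. Both are in cm. The difference of medians is a different location parameter, which equals the mean difference under symmetry. The valid objection is its lower power.
- A reader might infer that Bonferroni destroys the stated power. The number of comparisons is not given, and with one primary outcome the correction changes nothing. Even with two comparisons, power at 65 per arm is 82%; it falls below 80% only after attrition.

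The statement that the data are non-normal while recruitment is still running is minor. So is the pairing of thickness with stiffness, which occurs only in the imputation sentence. Treating per-protocol as co-primary is a convention, so its absence is not a contradiction.

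What the reply does not remove is the absence of any link to the margin. Two intervals or models are available, neither is designated, and choosing between them after the results are seen is what pre-specification should prevent. Nor is this detail left to an analysis plan: the section names the test, its sidedness, the correction and the analysis sets.

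**Conclusion.** The point holds as a contradiction within the protocol: the primary test does not test the primary hypothesis, and no decision rule uses the 0.31 cm margin on which the 51 per group rests. It must be corrected, because the trial's main conclusion depends on it.

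The error rates rest on normal data with the protocol's SDs and on non-significance being taken as non-inferiority. Under those conditions, a deficit equal to the margin passes about 5 to 11 times as often as the design allows (13% to 27% against 2.5%). The figures with Bonferroni rest on the further assumption of two comparisons.

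**What to change.** In the Statistical analysis section, state that non-inferiority is concluded if the lower limit of the two-sided 95% CI for the mean difference in postoperative quadriceps thickness (tourniquet minus non-tourniquet) lies above -0.31 cm. If the sponsor prefers a rank method, a Mann-Whitney test shifted by the margin, at one-sided 0.025, is acceptable at a small cost in power.

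Also:
- keep the unshifted Mann-Whitney test and the median difference as supportive analyses;
- remove Bonferroni for the single primary outcome;
- report the already planned per-protocol analysis against the same margin as a consistency check.

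The Primary outcome section measures both limbs before and after surgery. The limb, and whether the postoperative value or the change is analysed, are the sponsor's to state when the rule is written.

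The cost is a protocol amendment to the statistical section, made with 84 participants already recruited and communicated as the Auditing and amendments section requires. It needs no new data, and this point does not change N.
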